**CARERS**			
1	Psychological well-being	Depression Anxiety and Stress Scales (DASS-21)	Lovibond and Lovibond, 1995; SV: Bados et al., 2005
2	Expressed emotion	Family Questionnaire	Wiedemann et al., 2002; SV: Sepúlveda et al., 2014
3	Burden	Eating Disorders Symptom Impact Scale (EDSIS-S).	Sepúlveda et al., 2008; SV: Carral-Fernández et al., 2013
4	Accommodation to illness	Accommodation to Illness Symptoms Scale (AESED).	Sepúlveda et al., 2009; Quiles Marcos et al., 2016
5	Care skills	Caregiver skills scale.	Hibbs et al., 2015b; SV: Vintró-Alcaraz et al., 2018
6	Parents’ perception of efficacy	Parents vs anorexia.	Rhodes et al., 2005
7	Carer feedback form	Carers’ satisfaction and experiences in the study.	

*^1^Flett, G. L., Hewitt, P. L., Boucher, D. J., Davidson, L. A. and Munro, Y. (1997). The child-adolescent perfectionism scale: development, validation, and association with adjustment. Unpublished manuscript.*

##### Clinical Assessment

The health care providers at the day care center or the 24-h hospital unit will submit the following information on the patient: BMI from monthly clinical measurement and up to 9 months post-randomization, diagnosis, age at onset of disorder, evolution of illness over time (duration), admissions prior to current one, comorbidity and readmission after being discharged.

#### Carers

For carers the following outcome measures will be considered: emotional state, expressed emotion, impact from and accommodation to eating symptoms, coping skills, and parents’ perceived efficacy in dealing with the ED (see Table 1).

Patients and carers in the ECHOMANTRA-plus- TAU (treatment) arm will complete a “Participant Feedback Form.” It is a self-report measure created *ad hoc* for completion at the end of the intervention. It will assess participants’ experiences and satisfaction with the study. They will be asked to provide their views regarding: what they found beneficial and/or challenging, what they enjoyed and/or did not like, the transferability of ECHOMANTRA skills to their routine, and their suggestions for further improvements to the intervention.

### Blinding

Given the nature of the study design, all participants and therapists will be aware of the treatment condition.

The person responsible for creating the sequence of randomization will not belong to the research team and will not have other role in this research project. The researcher responsible for making the analyses will be a specialist in statistical methodology and only will participate in this aspect of the study. The research assistant who administers the assessment at each time period will not deliver the intervention. The statistician will be blinded to the condition allocated to the patient and their carer.

### Statistical Analysis

Firstly, a covariance analysis (ANCOVA) will be carried out using the pre-test scores as a covariate to analyze the impact of the combined intervention. Secondly, a repeated measures analysis of variance will be used to analyze the short and medium-term efficacy of the combined intervention in comparison to the usual intervention between and within groups at different time points, and effect size values will also be considered. Stratification will be performed in the analyses by the admission center and “diagnosis” variable will be controlled. IBM SPSS Statistics 24.0 will be used for all the analyses (IBM Corp, 2016).

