### Sample Size

An intention-to-treat method will be used to calculate sample size, considering the hypotheses for the primary outcome variables. Power calculations will be based on power determination for longitudinal designs with attrition (Hedeker et al., 1999), an alpha of 0.05, four assessment points (with baseline serving as a covariate), dropout rate of 40% and a fixed autoregressive coefficient of 0.40. A group size of 40 patients per group would provide 80% power with a bilateral *p* < 0.05 to detect a clinically significant change in eating pathology (overall Eating Disorder Examination Questionnaire, EDE-Q, of 0.45 points), assuming a standard deviation of one for the overall EDE-Q change scores (Hedeker et al., 1999), and also to detect a difference in mean weight gain of one Body Mass Index (BMI) point, which, based on previous research, would be clinically important to detect (Agras et al., 2000; Byrne et al., 2017). Therefore, if a sample loss of approximately 40% is taken into account, the participation of at least 70 participants per group will be required.

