##### Patients

Based on the interpersonal model of AN, the “MANTRA” part of the ECHOMANTRA intervention addresses patients’ modifiable characteristics, such as difficulties in emotional regulation, interpersonal relationships and eating. The intervention includes a workbook with an emphasis on specific behavioral change strategies. The workbook is organized into eight chapters that correspond to the contents of the eight sessions of the programme.

MANTRA will involved eight, weekly, individual online sessions lasting 60 min, which will be delivered by assistant psychologists trained by the first and principal authors of the study (YQ and [name]). During the sessions, the trained psychologist will encourage patients to reflect on the information and exercises proposed in the workbook. They will also carry out a series of activities taken from the MANTRA programme to further develop the contents included in the corresponding chapter of the workbook.

Each session will be themed following the structure of the patient workbook. Specifically, the focus of each session will be as follows: the first and second sessions will be on psychoeducation and motivation to change; the third session will be on skills to develop acceptance and self-compassion; the fourth and fifth sessions will be on skills to improve social functioning and to explore thinking styles; the sixth session will be on emotion management; and the seventh and eighth sessions will be on planning for the transition through goal setting, use of social support and implementation intentions.

For a more detailed description of the exercises, see Schmidt et al. (2014).

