##### Carers

Carers allocated to the intervention group will receive a carer workbook.

ECHO will involve eight, weekly, individual online sessions, lasting 60 min, which will be delivered by assistant psychologists trained by the first and principal authors of the study (YM and [name]). During the sessions, the trained psychologist will encourage discussion about the information and exercises proposed in the workbook. In addition, for a deeper understanding of the contents of each session presented in the workbook, carers will read and do activities from the book “Skills based caring for a loved one with an eating disorder: The New Maudsley Method” (Treasure et al., 2011). (Spanish version: Los trastornos de la alimentación: guía práctica para cuidar de un ser querido Treasure et al., 2011). These sessions will also include some of the video-clips from the Digital Versatile Disc (DVD) for carers “How to Care for Someone with an Eating Disorder”^1^. This DVD includes practical strategies and techniques to help carers develop skills and knowledge to help their loved one move toward recovery and to look after their own wellbeing by following the “New Maudsley Approach.”

This book and the DVD are designed to help carers develop self-reflective skills in order to develop confidence, compassion and the courage to take risks. Both resources will show them how to experiment with changes in their caring behavior so they can be more helpful to a loved one suffering from an eating disorder.

The workbook and online sessions will provide a skills training programme that includes training in stress management, communication (based on motivational interviewing techniques), strategies to reduce accommodation and expressed emotion and to increase extinction training and new habits at home *via* effective social support.

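### Possible clustering by psychologist, which can arise only in the ECHOMANTRA arm, is allowed for neither in the named analyses nor in the 80% power

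*Protocol article*

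**What the plan says.** The Randomization section allocates patient-carer dyads individually. In the ECHOMANTRA arm, the Patients subsection says: "MANTRA will involved eight, weekly, individual online sessions lasting 60 min, which will be delivered by assistant psychologists trained by the first and principal authors". The Carers subsection says the same of the carer component: "ECHO will involve eight, weekly, individual online sessions, lasting 60 min, which will be delivered by assistant psychologists trained by the first and principal authors". Under Treatment as Usual, controls receive neither the materials nor these sessions, and usual care comes from the centres' own teams in both arms.

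The Statistical Analysis section states: "Firstly, a covariance analysis (ANCOVA) will be carried out using the pre-test scores as a covariate to analyze the impact of the combined intervention". A repeated-measures ANOVA then covers the later time points. Centre (by stratification) and diagnosis (by control) are the only adjustments named.

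The Sample Size section states that "A group size of 40 patients per group would provide 80% power". The target difference is "overall Eating Disorder Examination Questionnaire, EDE-Q, of 0.45 points", "assuming a standard deviation of one for the overall EDE-Q change scores". The remaining inputs are a two-sided alpha of 0.05 and "four assessment points (with baseline serving as a covariate), dropout rate of 40% and a fixed autoregressive coefficient of 0.40". The only correlation in that list is correlation over time within a patient. The Blinding section keeps the statistician unaware of allocation.

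**The concern.** When several participants in one arm share a therapist and those in the other arm have no trial therapist, the design is partially nested. Both named tests assume that participants are independent. If psychologists differ, patients of the same psychologist resemble each other, the mean of the ECHOMANTRA arm varies more than the tests suppose, and the test rejects too often. A few unusually good or poor psychologists could then pass for an effect of the programme. That matters because the Discussion presents the programme as replicable in other settings.

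Adjusting for centre does not obviously deal with this. The sessions are online, the article does not tie psychologists to centres, and the psychologists work in one arm only.

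**Working it through.** **Inputs from the article (Sample Size).** Difference 0.45, SD 1, two-sided alpha 0.05, 40 per group, 80% power, autoregressive coefficient 0.40, four assessments with baseline as covariate (three post-baseline).

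**Step 1: reproduce the 80%.** Take the mean of the three post-baseline scores, with correlation 0.40 to the power of the lag, adjusted for baseline.
- Unadjusted variance of the mean: [3 + 2(0.40 + 0.40 + 0.16)]/9 = 0.547.
- Removed by baseline: [(0.40 + 0.16 + 0.064)/3]² = 0.208² = 0.043.
- Remaining variance v = 0.503.
- Standard error of the arm difference: √(2 × 0.503/40) = 0.159.
- Power = Φ(0.45/0.159 − 1.96) = 81%.

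The stated 80% is therefore reproduced with no therapist correlation at all. A single-time-point comparison with SD 1 would give only 52%.

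**Step 2: add clustering in one arm.** Let k be the number of psychologists, m = 40/k the caseload, and ICC the therapist intraclass correlation of the analysed outcome. Total variance is held equal in the two arms.
- Design effect, ECHOMANTRA arm only: DE = 1 + (m − 1) × ICC.
- Inflation of the variance of the arm difference: F = (1 + DE)/2.
- Type I error of the unadjusted test: 2[1 − Φ(1.96/√F)].
- Power of a test using the correct variance, set to exactly 80% at ICC 0: Φ(2.80/√F − 1.96).

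Example, k = 4 and ICC 0.05: m = 10, DE = 1.45, F = 1.225, √F = 1.107. Type I error = 2[1 − Φ(1.771)] = 7.7%. Power = Φ(2.531 − 1.96) = Φ(0.571) = 72%.

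**Step 3: range.** ICC and k are assumptions, because the article gives neither. All results are for 40 analysed per group.

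| ICC | Type I error, k = 2 / 4 / 8 | Power, k = 2 / 4 / 8 |
|---|---|---|
| 0 | 5.0 / 5.0 / 5.0% | 80 / 80 / 80% |
| 0.01 | 6.1 / 5.5 / 5.2% | 76 / 78 / 79% |
| 0.05 | 10.7 / 7.7 / 6.2% | 64 / 72 / 76% |
| 0.10 | 16.0 / 10.4 / 7.4% | 52 / 64 / 72% |

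At ICC 0.05 the true standard error exceeds the assumed one by a factor of 1.21, 1.11 and 1.05. A simulation of 20,000 trials per setting at ICC 0.05 gave type I errors of 10.3%, 7.5% and 6.1%, close to the formula. The power figures make no deduction for the few degrees of freedom that a therapist variance leaves, so they are somewhat favourable.

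**The case against.** **The harm is not established.** The article gives no ICC and no number of psychologists. Delivery is individual and follows a workbook with set session themes, and the Discussion calls the therapist guidance protocolised. None of this suggests a large therapist effect. This stands: at ICC 0.01 the loss is under 4 points even with 2 psychologists, and at ICC 0.02 with 3 or more it is under 5 points. A reader might infer that the standard errors are certainly too small. The article supports only the conditional statement.

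**The article is condensed and describes a pilot, and a fuller analysis plan may treat therapists.** This stands in part. However, the article does fix the two tests and the adjustment variables, and it states a power figure with its inputs. As written, these rest on independence within the ECHOMANTRA arm.

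**Random or fixed therapists is a choice of target.** If the conclusion were limited to the psychologists employed, the ordinary ANCOVA would need no inflation for them. This is correct, but the stated aim concerns the programme.

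**Two further readings go too far.** A reader might infer that patients and carers are pooled as independent observations. Their outcomes are listed separately, with one carer per patient, and nothing says that they enter one model, so within-dyad correlation does not bias the separate analyses. A reader might also put 70 per group into the formula and obtain larger error rates. But 70 already allows for about 40% loss, leaving 70 × 0.6 = 42 analysed, for which the results are close to those for 40.

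**A therapist identifier would unblind the statistician.** It would exist in one arm only, so this objection stands and shapes the fix.

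**Conclusion.** The point holds in conditional form. Psychologists deliver sessions in one arm only, and neither the named analyses nor the power inputs allow for outcomes being correlated within psychologist. Any positive therapist ICC makes the standard errors too small, in the patient analyses and separately in the carer analyses, and makes 80% an upper bound at 40 per group. The size ranges from negligible (ICC 0.01 with 8 psychologists: type I error 5.2%, power 79%) to serious (ICC 0.10 with 2 psychologists: 16.0% and 52%). These figures assume equal caseloads, one psychologist per participant, equal total variance in the two arms and 40 analysed per group. How psychologists are assigned to participants or centres is not stated. The point merits a change because the remedy is cheap and therapist identity is hard to recover afterwards.

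**What to change.** 1. Record which psychologist treats each patient and each carer.
2. In Statistical Analysis, add a partially nested mixed model: baseline score, centre, diagnosis and arm as fixed effects, a random psychologist intercept in the ECHOMANTRA arm only, and small-sample degrees of freedom such as Satterthwaite. Fit it separately to patient and carer outcomes.
3. If there are too few psychologists to estimate their variance, report the arm difference with its standard error multiplied by √F at fixed ICCs of 0.01, 0.05 and 0.10, using the actual caseloads. Base the conclusion about the programme on whether the result survives.
4. To keep the blinding, release the therapist identifier only after the blinded main analysis is locked, or have someone other than the blinded statistician run this step.
5. In Sample Size, state that the 80% assumes no clustering by therapist, and give the range in the table.

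The cost is one extra variable, some added text and one further analysis, with no more participants or staff. The downside is somewhat wider intervals, a less favourable stated power, and a therapist variance that will be imprecise with few psychologists.

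### The repeated measures ANOVA named for short and medium-term efficacy uses, without imputation, only patients with every visit, although the trial expects 40% dropout and was sized on a longitudinal model that allows for it

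*Protocol article*

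**What the plan says.** The protocol article, Statistical Analysis, sets out two steps. First, "a covariance analysis (ANCOVA) will be carried out using the pre-test scores as a covariate". Second, "a repeated measures analysis of variance will be used to analyze the short and medium-term efficacy of the combined intervention", comparing the arms between and within groups over time. The analyses are stratified by centre, control for diagnosis and run in SPSS 24. The section names no mixed model, imputation or analysis set.

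The Outcomes section fixes four assessments: T0 (baseline), T1 (post-intervention), T2 (3-month follow-up) and T3 (6-month follow-up).

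The Sample Size section works from a different model. It says "An intention-to-treat method will be used to calculate sample size" and that "Power calculations will be based on power determination for longitudinal designs with attrition". Baseline is a covariate, and the other inputs include a "dropout rate of 40% and a fixed autoregressive coefficient of 0.40". It arrives at 40 per group for 80% power to detect 0.45 EDE-Q points with SD 1, and asks for at least 70 per group to allow for loss. The Abstract gives 80 patients in total.

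**The concern.** Classical repeated measures ANOVA needs a complete set of outcomes from each patient. A girl seen at T0, T1 and T2 but not at T3 contributes nothing unless her missing value is imputed. With 40% dropout expected, the step that carries the short and medium-term question would rest on about 60% of those randomised and would ignore the partial follow-up of the rest.

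Two things are at stake. One is precision, because observed T1 and T2 data are thrown away. The other is the randomised comparison, because completers are a selected group. If selection acts differently in the two arms, the difference between completers is not the treatment effect. The article gives some reason to think about this. Participants know their arm, the experimental dyad receives eight patient and eight carer sessions that controls do not, and the Discussion anticipates difficulty in keeping the control group engaged.

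The stated method is also not the one that produced the sample size.

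**Working it through.** **Inputs from the Sample Size section.** Difference 0.45, SD 1, two-sided alpha 0.05, power 80%, autoregressive coefficient 0.40, baseline as covariate (so three post-baseline visits), 40% dropout.

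**Reproducing the 40.** The target is the average of T1 to T3.
- Variance of the average under AR(1): [3 + 2(0.40 + 0.40 + 0.16)]/9 = 0.547.
- Covariance of the average with baseline: (0.40 + 0.16 + 0.064)/3 = 0.208.
- Variance after baseline adjustment: V = 0.547 − 0.208² = 0.503.
- n per arm = 2V[(1.960 + 0.842)/0.45]² = 2 × 0.503 × 38.76 = 39.0. Rounded up this is 40, with power 81% at 40.

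Without the covariate, n = 2 × 0.547 × 38.76 = 42.4, and 42.4/0.6 = 70.6, close to the stated 70. A comparison at a single visit would need 2 × 38.76 = 77.5, that is 78 per arm. The stated sizes therefore come from a longitudinal model.

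**Power with complete cases.** Power = Φ(0.45/√(2V/n) − 1.960).
- 0.6 × 70 = 42 per arm: SE = √(2 × 0.503/42) = 0.155; 0.45/0.155 = 2.91; power 83%.
- 0.6 × 40 = 24 per arm: SE = 0.205; 0.45/0.205 = 2.20; power 59%.

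**Power with all available data.** Assume evenly spread monotone loss, so that 86.7%, 73.3% and 60% are seen at T1, T2 and T3. Adding each dropout pattern's information and inverting gives a variance per randomised patient of 0.667 for the same average.
- 70 randomised per arm: SE = √(2 × 0.667/70) = 0.138; power 90%.
- 40 randomised per arm: SE = 0.183; power 69%.

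Assuming one common effect across visits raises these to 92% and 72%. If all loss precedes T1, the variance is 0.503/0.6 = 0.839 and power returns to 83% and 59%, so there is no gain.

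**Selection bias.** Assume 40% loss after T1 in both arms. Dropout depends on the T1 score in one arm only, with log-odds 1 per SD; these slopes are not in the article. In simulation, completers in that arm shift by about 0.33 at T1, and the shift decays as 0.40 × 0.33 = 0.13 at T2 and 0.16 × 0.33 = 0.05 at T3. Differences between completers, for a true 0.45:

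| Visit | One arm affected | Other arm affected |
|---|---|---|
| T2 | about 0.31 | about 0.59 |
| T3 | about 0.39 | about 0.50 |

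Simulation runs vary by about 0.01; the decay formula gives 0.32 and 0.58 at T2, and 0.40 and 0.50 at T3.

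- Same dependence in both arms: 0.45 at every visit, no bias.
- Half the slope (0.5 in one arm, 0 in the other): about 0.37 at T2 and 0.42 at T3.
- T1 difference among everyone seen at T1: 0.45, no bias.

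These are differences between arms at each visit. Completers also differ at baseline by about 0.13, so bias in change from T0 is distributed differently: 0.32 + 0.13 = 0.45 at T2 (none) but 0.40 + 0.13 = 0.53 at T3, or 0.45 and 0.37 when the other arm is affected.

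**The case against.** The article does not state that patients with a missing visit are deleted. That follows from the named method when nothing is imputed, and a fuller plan, not shown here, could supply imputation and analysis sets. This stands, so the point is about the method chosen and not about an absent missing-data section.

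Several stronger readings are tempting but not supported:

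- A reader might infer that the ANOVA breaks an intention-to-treat commitment. The article attaches intention-to-treat only to the sample size calculation and promises no such analysis set.
- A reader might extend the bias to T1, where completers in the scenario differ by about 0.11 or 0.78. Those figures concern only the T1 level inside the ANOVA. The planned ANCOVA, read as a T1 analysis, needs only T0 and T1 and gives 0.45 here.
- A reader might infer that the trial is underpowered because of this choice. At 70 per arm, complete cases still give about 83% for the average effect. The low figure belongs to 80 in total, and the conflict between 80 and 140 is a separate matter.
- A reader might argue that including T0 as a repeated level dilutes the group effect. The article does not say that T0 is a level or that the group main effect is the test.

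The bias scenario is also strong: full dependence in one arm, none in the other. A mixed model recovers 0.45 there because dropout was made to depend on an observed score. None of this explains why the sizing and the follow-up analysis use different models, or what the ANOVA does with partial follow-up.

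**Conclusion.** The point holds as a mismatch between a named method and the trial's own sizing. The sample size allows for attrition and adjusts for baseline; the ANOVA, as named and without imputation, would discard every incomplete record.

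The cost in power is moderate at 70 per arm (about 83% against 90%) and larger if 80 in total are enrolled (about 59% against 69%). Both comparisons assume evenly spread loss and vanish if all loss precedes T1.

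The risk of bias concerns the follow-up estimates. It depends on dropout being related to symptoms differently by arm, which the article makes plausible but does not quantify. Its size and direction vary with the assumed slopes and with whether visit differences or changes from T0 are reported.

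**What to change.** Replace the repeated measures ANOVA with a likelihood-based mixed model (SPSS MIXED):

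- outcomes at T1, T2 and T3;
- baseline score, arm by visit, centre and diagnosis as fixed effects;
- all randomised patients with any follow-up, in their allocated arm.

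Name one contrast as primary; the T1 to T3 average matches the sizing. Add a sensitivity analysis for data not missing at random, for example a delta-adjusted one, and let it also address patients with no follow-up, whom this model still leaves out.

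The cost is a change of wording and slightly more analysis work, with no change to data collection. The model relies on a missing-at-random assumption, which the sensitivity analysis probes. The change should be fixed before outcome data are analysed, so that it cannot look data-driven.
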